#### 2.10.2. Sample Size for Second Phase

The second phase of the clinical trial will require a larger sample size. Upon reaching 156 participants, the initial results comparing the two psychotherapies (experimental and active comparator groups) will be published. The research methodology will remain unchanged, but the second phase aims to assess the effect of condition across four distinct groups (BATF for depression, BATF for anxiety, control for depression, and control for anxiety).

An Analysis of Variance (ANOVA) will be employed for this comparison. The sample size calculation for this phase requires a total of 472 participants. Therefore, an additional 316 participants need to be recruited, with 79 participants in each of the four groups. This requirement accounts for the data from the initial 156 participants, which will be included in the evaluations for the second phase to achieve the total sample size of 472 for comparison across the four groups.

The sample size calculation for Phase 2 was based on a 2 × 2 factorial design with four equally sized groups, assuming balanced allocation across conditions (*n* = 118 per cell in the final sample). The calculation maintained the same statistical assumptions as Phase 1. No formal interim adjustments were planned, and the design assumes complete case availability at the final analysis stage. Importantly, no attrition (dropout) rate was included in the sample size calculation, which may result in reduced effective statistical power if loss to follow-up occurs during the trial.

### 2.11. Statistical Methods

The primary analysis (Phase 1) will compare BATF versus Brief Focal Psychotherapy in a combined sample of participants with anxiety and/or depressive symptoms, irrespective of diagnostic category (“collapsed” clinical conditions). This analysis represents the primary confirmatory comparison of the trial.

Exploratory subgroup analyses within Phase 1 are pre-specified and will evaluate treatment effects separately in participants with anxiety and depressive symptoms.

The secondary analysis (Phase 2) will examine a pre-specified 2 × 2 factorial analytical framework (intervention × clinical condition), allowing assessment of main and interaction effects across four groups (BATF-depression, BATF-anxiety, control-depression, and control-anxiety), resulting in four analytical cells for the 2 × 2 factorial analysis.

For Phase 1, the primary comparison between BATF and Brief Focal Psychotherapy will be performed using Student’s *t*-test for normally distributed change scores or the Mann–Whitney U test when normality assumptions are not met. The first phase will include 156 participants.

Phase 2 will include a total sample of 472 participants (including participants from Phase 1 plus additional recruited participants). Change scores will be compared across the four predefined groups (BATF-depression, BATF-anxiety, control-depression, and control-anxiety) using one-way analysis of variance (ANOVA) or the Kruskal–Wallis test, as appropriate.

Assessments performed at Week 4 will be used to describe intermediate clinical evolution and may support exploratory analyses of treatment trajectories.

Effect Size Measure: Omega squared (ω^2^); Statistical Significance Level: α = 0.05.

Multiplicity for the co-primary outcomes will be controlled using the Holm–Bonferroni procedure. Secondary and subgroup analyses will be considered exploratory and interpreted accordingly. Exploratory biomarker analyses will apply false discovery rate (FDR) correction according to the Benjamini–Hochberg method.

Primary Analysis: Recruitment will be continuous, and allocation will follow a pre-generated 1:1 randomization sequence, stratified by clinical condition. Participants will be enrolled until the target sample size of randomized participants is reached. All analyses will follow the intention-to-treat principle. Missing outcome data will be handled primarily using maximum likelihood estimation within mixed-effects models. Multiple imputation may be performed as a sensitivity analysis, when appropriate, to evaluate the robustness of the findings.

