## 2. Methods and Analysis

### 2.1. Trial Design and Registration

This protocol was registered on 6 November 2024, in the Brazilian Clinical Trials Registry (ReBEC) under the identifier RBR-10p45rdg (https://ensaiosclinicos.gov.br/rg/RBR-10p45rdg, accessed on 11 June 2024), where the Statistical Analysis Plan (SAP) is available. The Universal Trial Number (UTN) is U1111-1313-4499.

This protocol was developed in accordance with the SPIRIT 2025 Statement. The completed SPIRIT 2025 checklist is provided as Supplementary Material S1.2.

This study is a single randomized controlled trial with blinded outcome assessment, blinded biomarker analyses, and blinded statistical analysis.

The trial has a 2 × 2 factorial structure, defined by two intervention arms BATF vs. Brief Focal Psychotherapy) and two clinical conditions (anxiety vs. depression), resulting in four analytical cells. Participants will be randomized in a 1:1 allocation to intervention arms, with stratification by clinical condition.

The trial includes two pre-specified analytical phases within the same randomized dataset. Phase 1 is the primary confirmatory analysis, comparing BATF versus Brief Focal Psychotherapy with clinical conditions collapsed. Phase 2 is a pre-specified secondary factorial analysis, evaluating the effects of intervention, clinical condition, and their interaction within the 2 × 2 framework. Both phases were defined prior to trial initiation and registered prospectively, with no adaptive modifications or interim decision-making based on Phase 1 results. Publication of Phase 1 results will not influence recruitment, eligibility criteria, randomization procedures, outcome measures, sample size targets, or statistical methods for Phase 2, which will continue according to the prospectively registered protocol.

The design allows estimation of overall treatment efficacy while also enabling pre-specified evaluation of differential effects across clinical conditions within a single randomized controlled trial framework.

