### 2.5. Outcomes

The objective of this study is to evaluate the effects of a brief psychotherapeutic intervention, BATF, compared with Brief Focal Psychotherapy in reducing symptoms of anxiety and depression.

Outcomes include quantitative measures of depressive and anxiety symptoms, sleep quality, and exploratory salivary and blood biomarkers associated with stress, inflammatory processes, and neurobiological function.

The co-primary outcomes for Phase 1 are defined as the change from baseline (Week 0) to Week 13 in symptom severity within each diagnostic stratum, assessed using disorder-specific scales (MADRS for depressive disorder and HAM-A for anxiety disorder).

Clinical diagnoses will be established during baseline psychiatric and clinical evaluation according to DSM-5-TR criteria prior to randomization. Participants will be stratified according to their primary clinical condition (anxiety or depressive disorder) and randomized to one of the two psychotherapeutic interventions. Each participant will be assessed only with the symptom severity scale corresponding to their primary diagnosis.

Secondary outcomes include depressive and anxiety symptom severity assessed using disorder-specific instruments according to participants’ primary clinical condition (PHQ-9 for depressive disorders and GAD-7 for anxiety disorders). Sleep quality, assessed using the Pittsburgh Sleep Quality Index (PSQI), and exploratory biomarker analyses will be performed in all participants.

Exploratory outcomes include salivary and blood biomarkers. Salivary biomarkers include cortisol, glutamate, immunoglobulin A (IgA), lysozyme, melatonin, alpha-amylase, chromogranin A, and fibroblast growth factor 2 (FGF2). Blood biomarkers include cortisol, pro–brain-derived neurotrophic factor (pro-BDNF), mature BDNF, sex hormones, dehydroepiandrosterone (DHEA), C-reactive protein (CRP), growth hormone, and glutamate. Cortisol and glutamate will be assessed in both saliva and blood samples. All biomarkers are pre-specified in the Statistical Analysis Plan and will be considered exploratory and hypothesis-generating.

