### 2.10. Sample Size

The standard deviation for the Montgomery-Åsberg Depression Rating Scale (MADRS) was estimated to be 11 [36]. The minimal clinically significant difference on the Montgomery-Åsberg Depression Rating Scale (MADRS) is considered to be 5 points. The minimal clinically important difference for the MADRS is not universally established and varies according to the estimation method and study population. Published estimates generally range from approximately 3 to 9 points, with values around 3–6 points considered among the most plausible across different methodological approaches. Therefore, a 5-point difference was adopted as a pragmatic mid-range estimate for sample size calculation purposes [37]. Alpha (α): a classical significance level of 5% is used, commonly applied in health research. A statistical power of 80% (β = 0.20) was adopted, as commonly recommended in health research.

The sample size was calculated based on the change in Montgomery–Åsberg Depression Rating Scale (MADRS) scores from baseline to week 13 (primary outcome). A two-sided significance level of 5% (α = 0.05), statistical power of 80% (β = 0.20), a clinically meaningful difference of 5 points, a standard deviation of 11, and a 1:1 allocation ratio were assumed. The calculation was performed using a two-sample *t*-test for independent means implemented in G*Power version 3.1.9.7. This corresponds to a standardized effect size of Cohen’s d = 0.45.

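### The Phase 1 confirmatory test is stated both as one collapsed comparison and as two Holm-controlled stratum co-primaries, with no common metric for the collapsed test

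*Protocol article*

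**What the plan says.** The protocol article describes the Phase 1 primary analysis in several places.

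- **Section 2.1** calls Phase 1 the primary confirmatory analysis, "comparing BATF versus Brief Focal Psychotherapy with clinical conditions collapsed". Section 2.2 repeats this for 156 participants.
- **Section 2.11** says the same: the comparison is made "in a combined sample of participants with anxiety and/or depressive symptoms, irrespective of diagnostic category", by t-test or Mann–Whitney test on change scores.
- **Section 2.5** defines co-primary outcomes for Phase 1 as "change from baseline (Week 0) to Week 13 in symptom severity within each diagnostic stratum", with MADRS for depressive disorder and HAM-A for anxiety disorder. It adds that each participant is assessed only on the severity scale for the primary diagnosis.
- **Section 2.11**, on multiplicity: "Multiplicity for the co-primary outcomes will be controlled using the Holm–Bonferroni procedure".
- **Section 2.11**, on the strata: "Exploratory subgroup analyses within Phase 1 are pre-specified and will evaluate treatment effects separately in participants with anxiety and depressive symptoms". It later says that subgroup analyses are interpreted as exploratory.
- **Section 2.10** labels MADRS change to Week 13 as the primary outcome and sizes Phase 1 on it: "a clinically meaningful difference of 5 points, a standard deviation of 11, and a 1:1 allocation ratio were assumed". Section 2.10.1 gives 77 per group, raised to 78 (156 in total).

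**The concern.** These statements cannot all hold. A single collapsed test leaves Holm nothing to adjust. Two stratum tests under Holm are neither collapsed nor exploratory. The analyses that section 2.5 makes co-primary appear to be the ones that section 2.11 calls exploratory.

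The collapsed test also lacks a defined outcome. No participant has both clinician-rated scales, so the only primary-scale data available for it are MADRS changes from some people and HAM-A changes from the rest. If these are pooled as they stand, the mean difference is in no single unit and cannot be compared with the 5-point MADRS difference behind the sample size.

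At stake is the trial's only confirmatory claim. Section 2.10.2 says that the initial results will be published once 156 participants are reached, so the first efficacy statement would rest on whichever reading is adopted.

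**Working it through.** **Inputs from the protocol:** two-sided alpha 0.05, power 80%, difference 5 and SD 11 on MADRS, 1:1 allocation (section 2.10); 78 per arm (section 2.10.1); no allowance for dropout (section 2.10.2).

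**Assumptions, not in the protocol:** a 50:50 stratum split in Phase 1 (39 per arm per stratum; 30:70 as a range), and the same standardised effect in both strata. The protocol gives no HAM-A difference or SD.

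**1. The plan's own figure.** d = 5/11 = 0.4545. The two-sample t-test (noncentral t) needs 76.95, so 77 per group. This reproduces the stated number.

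**2. Collapsed reading, standardised outcome.** With 78 per arm and d = 0.4545, power is 80.5%.

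**3. Holm reading, 39 per arm per stratum.** Power per stratum is 0.395 at alpha 0.025 and 0.509 at alpha 0.05.
- At least one: 1 − (1 − 0.395)² = 0.634.
- Both: 0.509² − (0.509 − 0.395)² = 0.259 − 0.013 = 0.246.
- With a 30:70 split, the stratum powers are 0.233 and 0.542 at 0.025, and 0.331 and 0.653 at 0.05. At least one: 1 − 0.767 × 0.458 = 0.649. Both: 0.331 × 0.653 − 0.098 × 0.111 = 0.205.
- For 80% power within a stratum, 77 per arm are needed at 0.05 (308 over two strata) or 94 per arm at 0.025 (376), against 156 planned.

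**4. How often the verdicts differ.** Take stratum statistics z1 and z2, each with mean 0.4545 × √(39/2) = 2.007, and a collapsed statistic (z1 + z2)/√2. In 2 million draws, the collapsed test and Holm at-least-one disagree in 20% of trials (18% with a 30:70 split and matching weights). Simulated t-tests give 21%.

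Neither reading is always the more favourable. With a 5-point effect in depression only, significance is 28% collapsed against 41% Holm at-least-one if the HAM-A SD is 11, and 35% against 41% if it is 8.

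**5. Type I error.** Under the null, the collapsed test gives 5.0% and Holm about 5% (1 − 0.975² = 4.9%). Counting success by either route gives 7.8%. The t-test simulation agrees: 4.8% + 2.9% = 7.7%.

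**6. Unstandardised pooling.**
- Equal standardised effects, HAM-A SD 8: the raw pooled t-test has 79.7% power, hardly below step 2.
- HAM-A SD 8, effect 2 points, mean change differing by 4 points between strata (all assumed): the pooled difference is (5 + 2)/2 = 3.5 and the SD about √((121 + 64)/2 + 2²) = 9.82, so d = 0.356 and power is about 59% to 60%.
- The same case on a standardised outcome: d = (5/11 + 2/8)/2 = 0.352, and power is again about 59%. The fall from 80% therefore comes from the smaller assumed HAM-A effect and not from mixing units.

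**The case against.** The two readings do not have equal support. Sections 2.1, 2.2 and 2.11 all name the collapsed comparison as confirmatory, and section 2.10.1 sizes Phase 1 as one two-group comparison. This stands: the text leans towards one test at 0.05. It still does not explain the co-primary definition or the Holm sentence.

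The statistical analysis plan, which is not shown, could hold a common metric. This also stands, and it makes raw pooling an inference: the article says only that change scores are compared. But a separate plan cannot remove a contradiction between the article's own sections.

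Four stronger readings are tempting but not supported.

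- **That the plan has an inflated type I error.** Either reading alone holds about 5%. The 7.8% needs a choice of route after seeing the data, which no section permits; the wording merely fails to rule it out.
- **That the trial has only 25% power.** That figure applies if both co-primaries must succeed, which no section requires. Holm would ordinarily allow a claim on either.
- **That mixing units costs much power.** Step 6 shows little loss in the cases tried. The damage is to the meaning of the estimate, and randomisation keeps the test valid under the null.
- **That the power figures are properties of the protocol.** They rest on an assumed stratum split and an assumed HAM-A effect.

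**Conclusion.** The contradiction is in the printed text and needs correcting before enrolment. Following the article exactly does not yield one primary verdict: the collapsed test, the Holm co-primaries and the MADRS-only primary outcome are three different targets, and the collapsed test has no stated metric.

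Under the stated assumptions (equal strata, effect 5/11 in both, no dropout), the planned 156 support a standardised collapsed test (about 80% power) but not the stratum co-primaries (about 63% for at least one, about 25% for both). The collapsed and Holm at-least-one verdicts part in roughly one trial in five. Type I error is at risk only if the route is chosen after the data are seen.

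**What to change.** Before first enrolment, make sections 2.1, 2.2, 2.5, 2.10 and 2.11 state the same confirmatory test on the same metric. Either of two routes reconciles them.

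**Option that keeps the collapsed intent and the 156.**
- Use one two-sided 0.05 test of the intervention difference in Week 13 change on the disorder-specific scale, standardised within scale by a stated SD, in a linear model with intervention, stratum and stratum-specific baseline.
- Report the MADRS and HAM-A differences in points, with 95% confidence intervals, as secondary.
- Remove the co-primary label and Holm from Phase 1.
- Restate the sizing assumption as a standardised difference on the chosen SD. The value 5/11 was set for MADRS change and does not carry over automatically, for example to scaling by baseline SD.

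**Option that keeps the stratum co-primaries.** Remove the collapsed and exploratory labels, say whether one or both must succeed, state HAM-A assumptions, and restate the power that 156 participants give.

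**Cost.** Wording changes to the protocol, analysis plan and registry; section 2.2 expects recruitment from the fourth quarter of 2026. Under the first option the primary estimate is in SD units, which are harder to read clinically, so the point-scale results by stratum must accompany it.

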### 2.4. Interventions

BATF, the experimental intervention in the present trial, will be delivered in a maximum of three sessions. BATF is an experimental psychotherapeutic intervention currently under evaluation in a randomized controlled trial, and has not yet been validated as an evidence-based treatment. Brief Focal Psychotherapy, which will serve as the active comparator group, may be conducted over a maximum of ten sessions, with sessions occurring once per week.

It is important to note that the difference in the number of sessions between BATF and Brief Focal Psychotherapy reflects the intrinsic structure and clinical logic of each intervention, and not an attempt to equalize treatment dose. BATF was designed as a highly structured, protocol-based brief intervention delivered in a maximum of three sessions, whereas Brief Focal Psychotherapy follows a more conventional brief psychotherapy format, typically delivered over several sessions. Therefore, the present trial compares two distinct models of brief psychotherapy as implemented in clinical practice, rather than interventions with pre-standardized or equivalent dose. This design allows for the evaluation of comparative effectiveness under real-world clinical conditions.

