#### Additional Analyses (Subgroup and Sensitivity)

As a sensitivity analysis, repeated-measures mixed-effects models may be conducted to evaluate the consistency of results across all assessment time points (baseline, Week 4, and Week 13), accounting for within-participant correlation.

Additional sensitivity analyses may include per-protocol analyses restricted to participants who complete the planned intervention and adjusted models controlling for baseline symptom severity, concomitant medication use, and treatment adherence (e.g., number of sessions attended), when appropriate. Post hoc exploratory analyses may be conducted as hypothesis-generating analyses if unanticipated patterns emerge.

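### The confirmatory Phase 1 test is an unadjusted comparison of change scores whose form depends on a normality check, and the optional adjusted models name sessions attended, which is tied to arm

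*Protocol article*

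**What the plan says.** Section 2.11 (Statistical Methods) makes the Phase 1 comparison of BATF with Brief Focal Psychotherapy the primary confirmatory one. The test is Student's t-test "for normally distributed change scores or the Mann–Whitney U test when normality assumptions are not met". The comparison is made "irrespective of diagnostic category (“collapsed” clinical conditions". No baseline covariate and no term for clinical condition is named. The same section says that "allocation will follow a pre-generated 1:1 randomization sequence, stratified by clinical condition".

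Section 2.5 (Outcomes) defines the co-primary outcomes as change to Week 13 in "symptom severity within each diagnostic stratum, assessed using disorder-specific scales (MADRS for depressive disorder and HAM-A for anxiety disorder". It adds: "Each participant will be assessed only with the symptom severity scale corresponding to their primary diagnosis".

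The subsection on additional analyses allows, as optional sensitivity analyses, "adjusted models controlling for baseline symptom severity, concomitant medication use, and treatment adherence (e.g., number of sessions attended), when appropriate". It also says that "repeated-measures mixed-effects models may be conducted to evaluate the consistency of results across all assessment time points". Section 2.4 caps BATF at three sessions, while Brief Focal Psychotherapy "may be conducted over a maximum of ten sessions, with sessions occurring once per week".

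**The concern.** Three features of the stated analysis need attention.

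- **No adjustment.** The change score subtracts baseline but leaves in whatever correlation remains between baseline and change. Collapsing over the stratification factor puts any stratum difference in mean change into the error term. Because the strata are measured on different scales, such a difference is to be expected.
- **A data-chosen target.** The t-test addresses a mean difference in points and the Mann–Whitney test a comparison of ranks. A preliminary check decides which is reported. The sample size in section 2.10 (5 points, SD 11) supports only the first.
- **A post-randomisation covariate.** Section 2.4 describes the unequal session numbers as part of how each therapy is built. Conditioning on sessions attended therefore removes part of what is being compared, and the arm coefficient becomes an extrapolation.

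At stake are power in a trial sized with almost no margin, a clear estimand, and the meaning of a sensitivity analysis.

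**Working it through.** **Inputs from section 2.10:** difference 5, SD 11 (taken as the SD of change), two-sided alpha 0.05, power 80%, 77 per group raised to 78. **Assumed, not in the document:** baseline to Week 13 correlation ρ, ratio k of baseline SD to Week 13 SD, stratum difference D in mean change, session distributions, effect per session, and the normality test (Shapiro on each arm).

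**1. The plan's own figure.** Noncentral t with d = 5/11 = 0.4545 gives 77 per group (power 80.0%), and 80.5% at 78. The stated size reproduces.

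**2. Baseline adjustment.** ANCOVA variance divided by change-score variance = (1 − ρ²)/(k² + 1 − 2ρk). Denominator minus numerator is (k − ρ)², so the ratio never exceeds 1. It equals 1 when k = ρ, and reduces to (1 + ρ)/2 when k = 1. The residual SD is 11 × √ratio. Power at 78 per arm:

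| k | ρ = 0.3 | ρ = 0.5 | ρ = 0.7 |
|---|---|---|---|
| 1.0 | ratio 0.65, 93.8% | 0.75, 90.3% | 0.85, 86.4% |
| 0.8 | 0.78, 89% | 0.89, 85% | 0.98, 81% |
| 0.7 | 0.85, 86% | 0.95, 83% | 1.00, 80.5% |

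**3. Omitting the stratum.** With equal strata the unadjusted SD is √(121 + D²/4). For D = 4 / 6 / 8 it is 11.18 / 11.40 / 11.70 and power is 79.3% / 77.7% / 75.5%, against 80.5% with a stratum term. Simulated type I error of the unadjusted test is about 4.0% at D = 6 and 2.8% at D = 10, so it is conservative.

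**4. The normality switch.** On normal data the Mann–Whitney test has relative efficiency 3/π. It would need 77/(3/π) = 80.6, so 81 per arm, and has about 78% power at 78. In simulation the check switches tests in about 9% of trials even when the data are normal. Type I error of the two-step procedure is 5.4% (normal) and 4.7% (skewed), close to nominal.

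**5. Sessions as a covariate.** BATF attendance is assumed uniform on 2–3, with the comparator uniform on the range shown. Variance inflation is 1/(1 − r²), where r is the correlation of arm with sessions. The last two columns assume 0.5 point per session within arm and a true arm difference of 5.

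| Comparator sessions | r | Variance inflation | Estimated difference | Power |
|---|---|---|---|---|
| 1–10 | 0.60 | about 1.5 | 6.4 | 83% |
| 4–10 | 0.84 | 3.4 | 7.2 | 59% |
| 8–10 | 0.98 | 24 | 8.1 | 16% |

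The shift is the per-session slope times the gap in mean sessions. In the middle row the gap is 7 − 2.5 = 4.5, so 5 + 0.5 × 4.5 = 7.25, in line with the simulated 7.2.

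**The case against.** Much of the defence is fair.

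- A reader might infer that the plan ignores baseline or inflates the false-positive rate. It does neither: the change score subtracts baseline, and simulated type I error is near or below 5%. The issue is efficiency and clarity of the estimand, not validity.
- A reader might infer that pooling two scales will probably fail the normality check. With 39 per stratum in each arm, SD 11 in both strata and mean differences of 4–8 points, the check switches in about 9–10% of trials, as it does without a mixture. With assumed SDs of 11 and 8 and differences of 4–10 points it switches in roughly 20–37%. The choice of test is left open, but a switch is not the expected outcome.
- A reader might infer that every adjusted model must include sessions. The text speaks of models in the plural, to be run when appropriate, with sessions as an example of adherence. A model without sessions is permitted, though none is specified. These models cannot alter the confirmatory result.
- Mixed models are named, both for missing outcome data in section 2.11 and as an optional repeated-measures sensitivity analysis. Neither names covariates, and neither replaces the stated t-test or Mann–Whitney test.
- The within-stratum co-primaries of section 2.5, with the Holm–Bonferroni procedure of section 2.11, would respect the stratification factor. But section 2.11 makes the collapsed comparison confirmatory and calls separate analyses by condition exploratory. The two sections conflict, so section 2.5 does not rescue the collapsed test.

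The analysis plan is said to be in the registry and may give more detail. The point rests on the test that the article itself fixes.

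**Conclusion.** The point holds as a recommendation to strengthen the analysis. The stated primary test is valid in size, but it leaves out two variables already collected and lets a preliminary check choose the estimand.

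The gain from baseline adjustment is never negative. It ranges from nothing (k = ρ = 0.7) to about 13 percentage points of power (k = 1, ρ = 0.3). Quoting only the equal-SD case of 86–94% would oversell it, because neither ρ nor k is in the document. The loss from omitting the stratum is small, 1 to 5 points of power for assumed stratum differences of 4 to 8.

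The sessions covariate is a separate flaw in an optional analysis. Its direction is clear, since the variable follows randomisation and has different caps by arm. Its size is not: variance inflation runs from about 1.5 to 24 depending wholly on assumed attendance, and the shift in the estimate depends on an assumed effect per session.

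**What to change.** - Pre-specify one primary linear model for Week 13 (ANCOVA or the equivalent repeated-measures model) with intervention, baseline score and clinical condition. Let the baseline slope differ by stratum, because the scales differ. Use robust standard errors and report the adjusted mean difference with its 95% confidence interval.
- Drop the normality-triggered switch and keep Mann–Whitney only as a fixed sensitivity analysis.
- Remove sessions attended from the adjusted treatment-effect models. State that the medication covariate is baseline medication, which section 2.3.2 already records, and not medication after randomisation.
- Reconcile the collapsed confirmatory test in section 2.11 with the within-stratum co-primaries in section 2.5. The choice matters: if Phase 1 split equally into 39 per arm in each stratum, a within-stratum unadjusted test would have about 51% power at alpha 0.05 and 39% at 0.025, under the plan's own difference and SD.

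No new data are needed. The cost is more than rewording an analysis plan: section 3 sends changes in statistical methods to the ethics committee for renewed approval and to the registry. Recruitment is expected from the fourth quarter of 2026, so the amendment should be made before then.

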Assessments will be conducted at baseline (Week 0), Week 4, and Week 13. The primary endpoint is defined as change from baseline (Week 0) to Week 13, and all outcomes will be analyzed according to the pre-specified statistical analysis plan using change-from-baseline metrics. Continuous outcomes will be summarized using group means and standard deviations or medians and interquartile ranges, depending on data distribution.

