#### 2.10.1. Sample Size Calculation for Initial Phase

To test the effect of BATF compared to the active comparator group, and to ensure sample homogeneity by clinical condition, the comparison of mean differences between the two groups is conducted. With the given parameters, the required sample size is 77 participants per group, totaling 154 participants. To account for the need to evenly distribute participants, 78 participants per group are necessary, resulting in a total of 156 participants.

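### Omega squared, the effect size fixed for the analysis, has no direction, is not in scale points and does not describe the rank tests the plan allows

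*Protocol article*

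**What the plan says.** Section 2.11 (Statistical Methods) plans a t-test on change scores for Phase 1, or the Mann–Whitney "U test when normality assumptions are not met". For Phase 2 it plans a one-way ANOVA over four groups, or Kruskal–Wallis. After both phases it states "Effect Size Measure: Omega squared", with no restriction to either phase or to any one test. The section names no between-arm difference with an interval and no rank-based effect size.

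Section 2.10 (Sample Size) works in points: "a 5-point difference was adopted as a pragmatic mid-range estimate for sample size calculation purposes". It then restates that difference in standardised form: "This corresponds to a standardized effect size of Cohen’s d = 0.45".

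Section 2.5 (Outcomes) gives the descriptive summaries: "Continuous outcomes will be summarized using group means and standard deviations or medians and interquartile ranges, depending on data distribution". It also has MADRS used for the depression stratum and HAM-A for the anxiety stratum, with each participant rated only on the scale that matches the primary diagnosis.

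**The concern.** Omega squared is an estimate of the share of outcome variance explained by group membership, built from ANOVA sums of squares. The primary question is comparative and two-sided: does BATF reduce symptoms more or less than Brief Focal Psychotherapy, and by how much relative to 5 points? A share of variance answers neither part directly. Because it is computed from raw-score sums of squares, it is also not an effect size for a test on ranks.

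What is at stake is how the result is read. A reader who has a p-value and omega squared cannot tell from them which arm did better, by how many points, or whether a non-significant result still leaves a 5-point difference plausible. The choice of test, the sample size and the error rate are not affected.

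**Working it through.** **Inputs.** From section 2.10: "a clinically meaningful difference of 5 points, a standard deviation of 11, and a 1:1 allocation ratio were assumed", with two-sided α of 0.05 and 80% power. From section 2.10.1: "the required sample size is 77 participants per group, totaling 154 participants", raised to 78 per group (156). SD 11 is given for MADRS; no SD is given for HAM-A.

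**The plan's own figure.** An exact noncentral-t calculation at d = 5/11 = 0.4545 gives 76.95, so 77 per group. Power is 80.0% at 77 and 80.5% at 78. The stated sample size is reproduced.

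**Direction.** For two groups of n = 78 (N = 156), with an observed difference of 5 and SD 11:
- t² = (5/11)² × 78/2 = 8.06
- sample omega squared = (t² − 1)/(t² + N − 1) = 7.06/163.06 = 0.043

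Only t² enters, so +5 and −5 both give 0.043. At no difference the estimate is −1/155 = −0.006; that negative value says nothing about which arm is ahead.

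**Scale.** The population value for two equal groups is d²/(d² + 4) = 0.2066/4.2066 = 0.049. Converting back, the unsigned difference is 0.4545 × SD: 5.0 points at SD 11, but 2.7 at SD 6, 3.6 at SD 8 and 5.9 at SD 13 (the SDs other than 11 are assumed). The conversion exists, but it needs the SD and the plan does not call for it.

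**Test.** Mann–Whitney and Kruskal–Wallis work on ranks. Omega squared from raw-score sums of squares does not describe what they test, so in the non-normal branch the stated measure and the stated test do not match.

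**What an interval in points would show.** The half-width is t(0.975) × SD × √(2/n).
- If all 156 participants shared one scale: SE = 11 × √(2/78) = 1.76, half-width about 3.5 points.
- With one scale per participant and an even split of strata (assumed; 156/4 = 39 per arm): SE = 11 × √(2/39) = 2.49, half-width about 5.0 points on MADRS.
- Range for the assumed split: if one third of participants are in the depression stratum (26 per arm), SE = 11 × √(2/26) = 3.05 and the half-width is about 6.1; if two thirds (52 per arm), SE = 11 × √(2/52) = 2.16 and the half-width is about 4.3.

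**Illustration at 39 per arm.** Suppose the observed MADRS advantage is 3 points for BATF. Then t² = (3/11)² × 39/2 = 1.45 and omega squared = 0.45/78.45 = 0.006. The interval for the advantage is 3 ± 5.0, from −2.0 to 8.0, so both zero and 5 remain plausible. A 3-point disadvantage gives the same 0.006, with an interval from −8.0 to 2.0, which excludes 5. Omega squared does not separate the two results; the interval does.

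**The case against.** The strongest reply is that the article is a condensed document. It points to a registered SAP that is not shown here, and an estimate with its interval is the kind of detail such a plan usually holds. Naming omega squared does not rule out reporting a mean difference as well. That is fair as far as omissions go. This point, however, concerns a measure that the article does state, placed beside analyses it does not fit.

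The second reply is that the article promises more than a p-value and omega squared. The numerator of the t-test is a signed difference, and group means and SDs with group sizes give direction, raw difference and an interval by simple arithmetic. This largely stands where means are reported. It leaves the reader to construct the interval, and it weakens in the non-normal branch, where medians and interquartile ranges may replace the means.

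Some stronger readings are tempting but not supported:
- A reader might infer that omega squared is the only effect size in the document. Section 2.10 also names Cohen's d, although only for planning.
- A reader might infer that omega squared can never be related to 5 points. With two equal groups and a known SD it converts to an unsigned difference, so the accurate statement is that it cannot be compared directly.
- A reader might blame omega squared for mixing the treatment effect with the anxiety–depression difference in Phase 2. A 5-point treatment effect and a 5-point condition difference do both give 0.049 across four groups, but this comes mainly from the one-way four-group ANOVA. In a 2 × 2 analysis omega squared can be computed per factor.
- A reader might infer that a non-significant result will be read as equal efficacy. Nothing in the document plans that.

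**Conclusion.** The point holds as a reporting defect in a stated choice. As written, omega squared covers the two-arm primary comparison, where it gives 0.043 for a 5-point difference in either direction (78 per arm, SD 11), carries no scale units, and does not match either rank test. Section 2.5 partly offsets this through group means and SDs, but it states no between-arm interval.

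A precision of ±3.5 points should not be quoted for this trial's MADRS result, because it would require all 156 participants to share one scale, and section 2.5 assigns one scale per participant. Under an even split the half-width is about 5.0 points, which rests on the assumed split, SD 11 and no dropout. No corresponding HAM-A figure can be derived, since no SD is given for it. The change is worth making before recruitment starts; it alters neither the sample size nor the tests.

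**What to change.** In section 2.11, replace the omega squared line for the treatment comparison with the following:
- The between-arm difference in change from baseline to Week 13 (BATF minus comparator) with a 95% CI, in MADRS points within the depression stratum and in HAM-A points within the anxiety stratum. State which sign favours BATF, and read the MADRS interval against the 5-point difference.
- A standardised difference with its 95% CI if the two scales are pooled for the collapsed comparison, since points on different scales cannot be averaged.
- If a rank test is used, a rank-based estimate such as the Hodges–Lehmann shift with its 95% CI.
- Omega squared kept, if wanted, only as a supplement to the Phase 2 ANOVA.

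If the registered SAP already specifies such estimates, align this line of the article with it. The cost is wording and minor reporting work. The estimates use the same data as the planned tests, and recruitment is not expected before the fourth quarter of 2026.
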